
**SHORT DESCRIPTION OF THE METHOD**

The surgical procedure consists of a laparoscopic bilateral radical fimbriectomy. The principle is to remove almost all of the tubes, from the uterine horn (at the level of the uterus because carcinomas develop on the distal part) to the fimbriae, by resecting the part of the ovary adjacent to the ovarian fimbriae (which adhere to the ovary). The purpose of this associated ovarian resection, which justifies its radical name, is to remove the two tube-peritoneal and tube-ovarian junctions, presumed to be the sites of the initial tumor events.

This leaves at least 2/3 of the initial ovarian volume in place on each side. The ovaries remain vascularized by their respective infundibulopelvic pedicles. The procedure is performed laparoscopically. An issue concerns hemostasis of the ovary left in place. A pilot series of 10 oophorectomy-completed radical fimbriectomies was performed using all laparoscopic means that combine hemostasis and tissue section. It appears that the use of EndoGIA-type linear staplers is the most effective method. The hemostasis of the ovarian cut section is complete with 3 rows of vascular staples. Sectioning with cold scissors followed by bipolar hemostasis of the remaining ovary part is also effective. Other methods (LigaSure® or Ultracision®) always result, to a greater or lesser extent, in epithelial burning and significantly alter the histological study. In addition, the quality of ovarian hemostasis is often imperfect and its revision leads to thermal damage to the remaining follicles that should be preserved. The routine use of EndoGIA 50 Forceps, vascular staples, is recommended.

## 6 INTRODUCTION AND STUDY RATIONALE

The identification, by linkage analysis in 1990 and then successive cloning of BRCA1 and BRCA2 genes in 1994 and 1995 disrupted the management of hereditary forms of breast and ovarian cancers. The molecular analysis of both genes now allows identification of a population of women at major risk of these cancers. More than 20,000 consultations and more than 9,000 tests for deleterious BRCA1/2 mutations were performed in France in 2009. Since 2003, the oncogenetic scheme has identified 8,488 people with a BRCA mutation [2009 INCa (*Institut national du Cancer* [National Institute of Cancer]) oncogenetic activity summary].

However, the cancer process remains multifactorial and penetrances are therefore highly variable. The cumulative lifetime risks are around 60 to 90% for breast cancers. For ovarian cancers, these risks are around 40% for BRCA1 and 20% for BRCA2. The mean age of onset is also later for BRCA2. The probability of these cancers occurring before the age of 50 is 5%-10% for BRCA1 and 1%-5% for BRCA2 [Chen 2007; Robson 2007]. The risks vary depending on the number of cases and age of occurrence in families [Metcalf 2010]. The baseline test is usually performed in an affected person to optimize these tests, which remain complex and expensive with waiting times for results of several months. The predictive test in asymptomatic patients leads to the identification of major breast and ovarian cancer risks and without known equivalent. For breast cancer risk, the majority of women choose specific screening (by MRI) given the physical and psychological consequences of bilateral mastectomy. The situation is different for pelvic risk, as we do not have an effective screening method but a less unacceptable preventive surgical solution than preventive breast surgery, especially in postmenopausal women. The seriousness of ovarian cancers, well known by clinicians as well as women who have had a case in the family, means that most mutated women will opt for preventive adnexal surgery, with or without hysterectomy. It is increasingly clear that adnexal preventive surgery provides the best risk-benefit in this situation with a reduction in both pelvic and breast cancer risk [Domchek 2010].

However, the consequences of castration should be considered in young women. Known over both the short and long-term, they can be improved with estrogenic or estrogen-progestin hormone replacement if the uterus is preserved. Short-term replacement therapy does not seem to prevent reduction significantly in a castration-related breast cancer risk reduction study [Rebeck 2005]. However, this treatment is contraindicated in women who have previously had breast cancer. Many mutated women are reluctant to undergo, or delay, ovarian surgery. In the French GENEPSO (*Gène étude prospective sein ovaire* [Ovary breast prospective gene study]) cohort, only 55% of women without disease and 62% of women with breast cancer over 40 years of age opted for adnexal surgery.

**The decision for pelvic preventive surgery is therefore particularly difficult in young mutated women, especially for deleterious BRCA1 mutations given the greater pelvic risk, and even more in women who have had breast cancer previously, for whom hormone replacement treatments are contraindicated.**

We tried to improve the effectiveness of screening for pelvic tumors by bringing the examinations closer together and performing an ultrasound every 6 months by a trained physician and a CA-125 assay. This study, conducted as part of a PHRC (*programme hospitalier de recherche clinique* [clinical research hospital program]) in 2003, confirmed, consistent with all of the literature on the subject, the lack of utility of screening in these hereditary forms since the two tumors identified out of the 72 assessable patients were peritoneal carcinosis [Taieb 2011].

However, new elements have come to modify the natural history design of ovarian tumors.

**Alongside the increase in the number of preventive adnexal surgeries and the increased attention of pathologists to the specimens entrusted to them, it appeared that a significant number of the occult precancerous lesions occurred not on the ovary but on the tube and especially on the uterine horn.**

Detailed pathological studies of prophylactic adnexectomy specimens of BRCA1/2 mutated women have revealed the common presence, apart from any invasive process, of serous tubal intraepithelial carcinomatous lesions (or STIC for *Serous Tubal Intraepithelial Carcinoma*) [Lee 2006; Crum 2010]. These abnormalities were also found, adjacent to invasive lesions, in the tubes of patients operated on for sporadic high-grade serous ovarian or peritoneal carcinoma. Another important anatomical feature is that these intraepithelial lesions are mainly found in the fimbrial end of the tube (or **fimbriae**). Immunohistochemical studies of the fimbrial ends of the fallopian tubes in apparently healthy BRCA mutated patients have shown that their cells often have high concentrations of the TP53 protein. This high concentration is caused by a non-functional protein and usually reflects abnormalities in the p53 gene (mutation, overexpression, etc.). This concentration abnormality has been named "signature p53" [Lee 2006]. Its discovery could precede the onset of transitional intraepithelial tubal lesions and STICs [Crum 2010]. However, their specificity is more doubtful because p53 signatures have been found in healthy tubes or even outside the tubes and also in women without a genetic context.

The hypothesis of dissemination of these abnormal tubal cells on the ovarian cortex or in its inclusion cysts, then their development into carcinoma, is supported by very recent biomolecular studies. They indeed confirm the expression by high-grade serous cancer cells of Müllerian markers (such as the tube) and non-mesothelial markers (such as the ovarian cortex) [Kurman 2010]. This would therefore be a matter of serous high-grade carcinomas, of secondary carcinogenesis of the ovary through the tube, and not primary ovarian tumor. According to Kurman, type 1 lesions would thus originate in the carcinogenesis of post-ovulation inclusion cysts, which, when healing the ovarian defect, would therefore include Müllerian tissue. The type of carcinoma then depends on the origin of these Müllerian cells. Thus, inclusion cysts with tubal-derived cells may cause low-grade serous carcinoma, either from the outset or after a stage of serous borderline tumor. If the cells are of endometrial origin (directly by menstrual blood reflux, or indirectly through endometrial injury), they may produce endometrioid carcinomas or some clear cell carcinomas [Kobayashi

2009]. Cells of endocervical origin may also cause clear cell carcinomas. Finally, although a more hypothetical mechanism, paratubal cells, located at the junction between the fimbriae and ovarian epithelium, would give rise to mucinous carcinomas and degenerated Brenner tumors, which would otherwise be precursors [Kurman 2010].

The various forms of ovarian carcinoma could therefore be categorized into two main anatomic/clinical and prognostic types [Shih 2004]. Schematically, type 1 would be slow-growing tumors, so more often found in the early stages. It includes low-grade serous, mucinous, grade 1 to 2 endometrioid and clear cell carcinomas. These tumors have specific molecular abnormalities, all of which focus on mitotic signaling or cell survival pathways (KRAS (mucinous), BRAF, HER2 (low serous grade), PTEN and beta-catenin (endometrioid), PI3K-AKT (clear cells) [Gilks 2010; Despierre 2010]. They have stable genetics and few p53 mutations in common. In contrast, type 2 tumors are high-grade serous or endometrioid carcinomas [Geyer 2009], carcinosarcomas, and undifferentiated carcinomas. These lesions usually progress rapidly, despite a good initial response to medical treatment. At the biomolecular level, they only very rarely have abnormalities in mitotic signal transduction or survival, but present from the outset with various genetic alterations of the p53 gene, causing an ineffective protein to trigger the repair of altered DNA or, failing that, cellular apoptosis. These differences thus suggest different origins and development modalities of these 2 tumor types. It is hypothesized that type 2 tumors mostly originate in the tube and are now rather grouped together as **serous pelvic carcinoma** that no longer indicates their ovarian or primary peritoneal tubal origin. **Most of the pelvic tumors associated with BRCA1/2 would be type 2. This reminds us that pathologists have long been perplexed about the origin of ovarian tumors, which have so far had no identified precursor and studies that have shown, at least for some, a reduction in pelvic risk through tubal ligation. These facts would also explain the ineffectiveness of screening for these initially tubal and rapidly ovarian and peritoneal proliferative tumors.**

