#### ***All criteria are required for inclusion:***

- Women over 35 years of age
- After completion of the pregnancy
- BRCA 1 or 2 mutation, or family breast/ovarian documented by genealogy
- Not ready for bilateral adnexectomy (procedure that will always be routinely offered 1st)
- Involvement or not of breast cancer
- Affiliated with a social security plan

- Informed consent and signed by the patient prior to implementation of any study-specific procedures

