### **8-7 Endpoints**

#### **8-7-1 Pelvic cancer**

The cumulative incidence of pelvic cancer will be estimated by measuring the time-to-onset of pelvic cancer, defined as time from the date of the fimbriectomy to the date of the ovarian cancer, high-grade primary peritoneal cancer, or cancer of other gynecologic pelvic location, with death without pelvic cancer considered a competitive event. Study withdrawal for oophorectomy is also a competitive event. Patients alive without pelvic cancer or oophorectomy based on most recent information are censored at this time.

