### **8-8 Statistical methodology**

#### **8-8-1 Determination of the number of patients and study discontinuation criteria**

The cumulative incidence of pelvic tumors is estimated to be around 10% at 10 years in BRCA mutated women in the absence of prophylactic surgery (Chen et al Meta-analysis of BRCA1 and BRCA2 penetrance JCO 2007; 25:1329-33), corresponding to an “acceptable” rate of 3% at 3 years. A dynamic method for interim analyses for rare events will be used to discontinue the study if, within 3 years, the number of pelvic tumors reaches 2 for 12 participants, 3 for 27 participants, 4 for 46 participants, and 5 for 66 participants for a maximum number of patients of 120 (Kramar A, Bascoul-Mollevi C. Early Stopping Rules in Clinical Trials Based on Sequential Monitoring of Serious Events. Med Decis making 2009;29:343-350). These decision rules correspond to the comparison of the lower limit of the confidence intervals adjusted on the information fraction and on a concave alpha spending function. Three years after the last patient is enrolled, if 8 pelvic tumors are observed among the 120 patients, the treatment strategy will be considered insufficiently promising as the lower limit of the one sided 90% confidence interval will not contain the acceptable value of 3%.

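### The 3%-at-3-years benchmark is a no-surgery carrier rate at the top of the protocol's own before-50 range for BRCA1 and above that for BRCA2, so the stopping and final rules lean toward not declaring failure

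*Protocol*

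**What the plan says.** **Benchmark.** Protocol section 8-8-1 (repeated in the synopsis) states: "The cumulative incidence of pelvic tumors is estimated to be around 10% at 10 years in BRCA mutated women in the absence of prophylactic surgery". It converts this to an acceptable "rate of 3% at 3 years".

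**Rule.** The study stops early at 2 tumors in 12 participants, 3 in 27, 4 in 46 or 5 in 66. At the end, "if 8 pelvic tumors are observed among the 120 patients", the strategy is judged insufficiently promising because "the lower limit of the one sided 90% confidence interval will not contain the acceptable value of 3" (per cent). No criterion for success is given.

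**Risk figures in the rationale.** Section 6, citing the same meta-analysis together with a second source, states: "The probability of these cancers occurring before the age of 50 is 5%-10% for BRCA1 and 1%-5% for BRCA2". It puts lifetime risk at around 40% (BRCA1) and 20% (BRCA2).

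**Cohort and endpoint.**
- Women are over 35, with no upper age limit (section 8-2), not postmenopausal at entry (8-3), and followed until menopause (8-5).
- Genetic eligibility is "BRCA 1 or 2 mutation, or family breast/ovarian documented by genealogy".
- For the primary endpoint, "Study withdrawal for oophorectomy is also a competitive event" (8-7-1).

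**The concern.** The benchmark describes mutation carriers who have no surgery. The trial population differs in three respects, and the protocol does not adjust for any of them.

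- Much of the time at risk falls before about age 50. Section 6 gives the whole risk up to that age as 5–10% or 1–5%, depending on the gene.
- Some women may enter on family history without a documented mutation.
- Secondary oophorectomy is part of the plan (section 6-2), and it removes women from risk.

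If the untreated risk in this cohort is below 3% at 3 years, a boundary built on 3% will rarely be reached even when fimbriectomy prevents nothing. A low tumor count could then be read as reassurance that the design cannot give.

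**Working it through.** **1. The protocol's own figures reproduce.** 10% × 3/10 = 3.0%; with a constant hazard, 1 − 0.9^(3/10) = 3.11%. Expected cases: 0.03 × 120 = 3.6. The exact one-sided 90% lower limit is 3.92% for 8/120, so 3% is excluded. It is already 3.27% at 7/120.

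**2. Three-year untreated risk from section 6.** Let R be the risk before 50 and W the years over which it accrues. W is assumed: 15 for ages 35–50, or 10 if all of it falls between 40 and 50. Risk = 1 − (1 − R)^(3/W).

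| | R | W = 15 | W = 10 |
|---|---|---|---|
| BRCA1 | 5% | 1.02% | 1.53% |
| BRCA1 | 10% | 2.09% | 3.11% |
| BRCA2 | 1% | 0.20% | 0.30% |
| BRCA2 | 5% | 1.02% | 1.53% |

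**3. Mixed cohort.** The gene mix is assumed.
- Lowest case (50:50, W = 15, low ends): 0.5 × 1.02 + 0.5 × 0.20 = 0.61%, or 0.7 cases per 120.
- Highest case (70:30, W = 10, high ends): 0.7 × 3.11 + 0.3 × 1.53 = 2.64%, or 3.2 cases per 120.

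Only an all-BRCA1 cohort at the top of its range, with all the risk in one decade, reaches 3%.

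**4. How often the rules declare failure if the operation does nothing.** This is an exact binomial recursion through 2/12, 3/27, 4/46, 5/66 and 8/120, treating every woman as observed for 3 years.

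| True 3-year risk | P(8 or more of 120), no interim looks | Failure at any look |
|---|---|---|
| 1.0% | below 0.0001 | 0.008 |
| 1.55% | 0.0006 | 0.023 |
| 2.1% | 0.004 | 0.048 |
| 2.6% | 0.014 | 0.086 |
| 3.0% | 0.029 | 0.120 |

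Even at exactly 3%, an ineffective operation escapes the failure verdict 88% of the time, because the acceptable rate is itself the no-surgery rate.

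**5. Effect on the final boundary.** The first count of 120 whose exact one-sided 90% lower limit exceeds the benchmark is 4 for 1%, 5 for 2.0%, 6 for 2.1% and 7 for 3%. The protocol uses 8.

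**6. Oophorectomy as a competing event.** With hazards h = −ln(0.9)/10 = 0.0105 for cancer and g for oophorectomy, cumulative incidence = h/(h + g) × (1 − exp(−(h + g)t)). If 20% have oophorectomy by 3 years (assumed), g = −ln(0.8)/3 = 0.0744. The 3-year incidence is then 2.79% rather than 3.11%, about 0.3 points lower. If 50% have it by 10 years (assumed), the 10-year figure is 7.3% rather than 10%.

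**7. Risk after 50.** Assume lifetime risk is reached at 70 and the before-50 risk is at the top of its range. Three-year risk is then 1 − (0.60/0.90)^(3/20) = 5.9% for BRCA1 and 1 − (0.80/0.95)^(3/20) = 2.5% for BRCA2. Older participants would therefore raise the cohort figure.

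**The case against.** A reader might infer that 10% exceeds the protocol's own risk figures outright. It does not: 10% is the upper end of the BRCA1 range, and the most concentrated case returns 3.1% at 3 years. There is no upper age limit, and risk after 50 is higher. Section 6-2 expects a substantial proportion of women with BRCA1-related breast cancer, which suggests a BRCA1-rich cohort. The documents give no age or gene distribution and no risk for women without a documented mutation. Section 6 cites two sources, so the ranges cannot be assigned to one of them. All of this stands, and it limits the claim to assumed mixes.

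A reader might also infer a bias toward success. The protocol has no success rule, so the bias is only toward not declaring failure.

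Nor is it wrong to count oophorectomy as a competing event. It is a valid and openly stated estimand, and oophorectomy incidence is reported as well. The fault lies only in the comparison with a no-surgery rate. The 3-year effect is small and the oophorectomy rates are assumed. The drop from 10% to 7.3% is at 10 years and touches no stated decision.

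Some features work in opposite directions. The endpoint includes other gynecologic pelvic sites, which raises the count; excluding women with STIC or invasive cancer on the specimen lowers it. The planned analysis by attained age (section 8-8-2) helps description but names no comparator.

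**Conclusion.** The concern holds in this limited form. Sections 6 and 8-8-1 are not reconciled, and the benchmark sits at the top of the BRCA1 range and above the BRCA2 range. Under 50:50 to 70:30 BRCA1:BRCA2 mixes, and with risk spread over 10 to 15 years before 50, the protocol's own figures give 0.6–2.6% at 3 years instead of 3%. At 1.0–2.1%, an operation with no effect would be declared a failure about 1–5% of the time, and at 2.6% about 9%. The competing-event mismatch adds roughly 0.3 points at 3 years in the same direction and grows with longer follow-up. The size depends on the age and gene mix, which the documents do not give; a BRCA1-rich or older cohort would narrow or remove the gap.

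**What to change.** 1. Reconcile the before-50 figures in section 6 with the 10% at 10 years in section 8-8-1, and justify the benchmark for the age and gene mix actually enrolled.
2. State that staying below 8 of 120 does not show benefit, because the acceptable rate is the rate expected without surgery.
3. Add an observed/expected analysis in mutation carriers. Sum age- and gene-specific untreated rates from the cited meta-analysis over each woman's person-years with ovaries in place, up to oophorectomy or last news. Report the ratio with an exact Poisson interval, and show women without a documented mutation separately.
4. Keep the competing-risk curve as the descriptive estimate.

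**Cost.** This is one further analysis using age, mutation status and dates, with no change to conduct. The benchmark becomes lower and less favourable, and the analysis would be specified after recruitment closed. Precision at 3 years is poor. With zero cancers observed, the exact two-sided 95% upper limit for the count is −ln(0.025) = 3.69, so with 3.2 expected the ratio's upper limit is 3.69/3.2 = 1.15, and higher with fewer expected. It is informative mainly over the longer follow-up, which is projected to 2034.

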- This solution also allows for a potential, even theoretical, preservation of fertility since medically assisted reproduction techniques could be considered later in these cases.

## **6-2 Potential disadvantages of radical fimbriectomy [Greene 2010]**

- The rate of pelvic tumors that develop from the tube is not precisely known, and the benefit for these women will obviously be proportional.
- The idea is to perform castration afterward, closer to the natural age of menopause, and this will require a second pelvic procedure. Some women may not want to consider this second surgery, in the hope of a sufficiently reduced risk by removing the tube.
- The potential drawback that seems most important to us is the lack of reduction in breast cancer risk through ovarian suppression. Castration is generally known to reduce the risk of breast cancer, particularly tumors with steroid receptors. It is more than likely that this risk reduction is through ovarian hormone suppression. The studies confirm this risk reduction for women who have a BRCA1 and BRCA2 mutation [Rebbeck 2009]. However, it should be noted that in prospective studies this reduction in breast cancer risk is greater for BRCA2 mutations than BRCA1, which is not unexpected given the large proportion of tumors without BRCA1 receptors. However, the absence of a receptor may not necessarily reflect complete independence of the tumor from sex hormones. It should also be noted that these studies are observational and subject to risks of bias that are not always easy to identify or correct; therefore, the estimate of breast cancer risk reduction is only approximate [Heermskerk 2010]. One can also argue about the possibility of replacement therapy after castration; however, this treatment is contraindicated in breast cancer and some studies show that this treatment may not be as

effective as natural hormonal impregnation [Rebbeck 2009]. A substantial proportion of women who will be enrolled will likely have a history of BRCA1-related HR- breast cancer and the influence of castration on contralateral cancer risk is not really documented [Domchek 2010].

All of these arguments justify a prospective study of bilateral radical fimbriectomy that may help to better understand the risk-benefit ratio in this complex and very personal choice, but also to better understand the natural history of high-grade pelvic tumors that are obviously not just the prerogative of BRCA 1/2 mutations.

## 7 STUDY OBJECTIVES

### 7-1 Primary objective

- To assess the **incidence** of pelvic serous cancer after prophylactic radical fimbriectomy in women at hereditary risk of pelvic serous cancer, but not ready for prophylactic adnexectomy

